**Fig. 2 Fig2:**
[figure not shown]
ADR Stage 2 Adjudication Agreement Matrix

### Statistical methods

The intention-to-treat study population will consist of all subjects who are randomized. The per-protocol population will consist of those subjects who have at least 60% of the SENATOR report STOPP recommendations acted on by the clinical team. The safety population will include all subjects who provide informed consent.

The primary analysis will compare the odds of subjects in the SENATOR intervention and control groups experiencing the primary endpoint as defined above using a multiple logistic regression in the intention-to-treat population, and adjusting for strata used in the randomization (medical versus surgical admissions and study recruitment site). The null hypothesis is that there is no significant difference between control and SENATOR intervention groups in the adjusted odds of experiencing the primary endpoint. The corresponding estimated effect size will be reported as an odds ratio (SENATOR: control) with 95% confidence intervals. Secondary endpoint analyses will use a similar approach. The null hypothesis will be rejected if this confidence interval excludes the null odds ratio of 1.0. Relevant individual and aggregate data on study related deleterious events will be presented.

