## Background

Adverse drug reactions (ADRs) represent a significant and growing global healthcare problem, especially in the elderly population. ADRs may both cause hospitalization, and/or occur in hospital. Approximately 11% of hospital admissions in adults aged ≥65 years are caused by ADRs [1], while one in ten hospitalised patients are reported to experience an ADR during their inpatient stay [2]. Older age [2], female gender [3], multi-morbidity [4], polypharmacy [4] and frailty [5] are significant predictors of ADRs and are central to the GerontoNet ADR prediction tool described in 2010 [6]. Since approximately half of all ADRs are thought to be preventable [7], they represent a major, modifiable contributor to morbidity and mortality in older subjects.

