### Allocation concealment

Trial allocation is delivered using an interactive Web-Response System developed in conjunction with the main trial database by Clininfo®, the data management partner company within the SENATOR project. Subject allocation is released once all necessary baseline information data have been entered into the trial database and a decision is made to randomize. In subjects randomized to the active intervention, trial data are automatically transferred to the cloud based SENATOR software engine maintained by Clanwilliam Health®, and the resulting SENATOR report is automatically emailed to the local trial research staff at a designated email.

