### Data management

Although pragmatic and using a ‘real world’ approach to the dissemination of the SENATOR report and with a variable degree of engagement by the clinician, it has been necessary to develop and use a trial specific database to gather the inputs used by the SENATOR software in a standardized fashion from the different countries and to collect the trial outcome data which are collected to a far greater degree of precision and accuracy than is usual in clinical practise. To this end, data are entered electronically by the local site research staff into a cloud based database developed by Clininfo®. Data collected is pseudo-anonymized and includes baseline past medical history, current prescription medications and doses, routine blood biochemistry and haematology laboratory data, baseline ECG data, cognitive assessment using the Mini-Mental State Examination [16], functional assessment using the Barthel Index [17], and health related quality of life using the EQ-5D-5 L [18]. At day 14 post randomization or at discharge, whichever occurs first, the EQ-5D-5 L is repeated, the subjects medical conditions reviewed and medications recorded. The case records are reviewed to assess the number of SENATOR recommendations that have been adopted and to identify any potential endpoints as discussed below. At discharge arrangements are made with participants and/or their family for a 12 weeks (+/− 4 weeks) post hospital discharge follow-up call by the local site research staff. This is to enquire about healthcare utilization and any re-hospitalization since the index hospitalization, changes in medications and current health related quality of life.

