### Sample size

In a recent single blinded trial of the manual application of STOPP/START criteria, conducted at the coordinating investigator site, the observed control group hospital-acquired ADR incidence was 21% compared to an ADR incidence of 11.5% in the intervention group, equivalent to an ADR odds-ratio of 0.45 [8]. This study had similar entry criteria and primary endpoints to the current trial, but differed in that the STOPP/ START recommendations were manually generated and then directly discussed and reviewed with the primary team by a specialist registrar (senior resident) in geriatric medicine. To be conservative, and in view of the more rigorous ADR adjudication processes, we have based our power calculations for the current trial on a lower control group event rate (18%) than that seen in our earlier trial, and we assume a reduced effect size (an odds ratio of 0.65) in order to reflect the potential reduced uptake of recommendations by clinicians. Based on these assumptions, using the method of Farrington and Manning for a trial to test the difference between two binomial events with a two-sided type 1 error rate of 0.05, we achieve 90% power with the proposed recruitment of 900 subjects per trial arm. The planned CONSORT flow diagram for the trial is shown in Fig. 3.

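### The primary model adjusts for site and admission type only; adding a short pre-specified list of the ADR predictors the article itself names would raise power modestly at almost no cost

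*Protocol article*

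**What the plan says.** Under Statistical methods, the protocol article compares the arms "using a multiple logistic regression in the intention-to-treat population", "adjusting for strata used in the randomization (medical versus surgical admissions and study recruitment site"). The result is an odds ratio with a 95% confidence interval, and the null hypothesis is rejected if the interval excludes 1. The secondary endpoints are to be handled similarly. No other covariate is mentioned for the primary model.

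Three other places bear on that choice:

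- Background: "Older age [2], female gender [3], multi-morbidity [4], polypharmacy [4] and frailty [5] are significant predictors of ADRs".
- Data management: the data collected "includes baseline past medical history, current prescription medications and doses, routine blood biochemistry and haematology laboratory data", together with an ECG, the Mini-Mental State Examination, the Barthel Index and the EQ-5D.
- Allocation concealment: "Subject allocation is released once all necessary baseline information data have been entered into the trial database".

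Under Sample size, the design assumes an 18% control rate, an odds ratio of 0.65 and a "two-sided type 1 error rate of 0.05", and concludes that "we achieve 90% power with the proposed recruitment of 900 subjects per trial arm".

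**The concern.** The article identifies patient-level predictors of the outcome and records them, or measures of them, at baseline. It then confines the primary model to the two stratification factors. Site and medical or surgical admission cannot capture differences in age, drug count or function between patients within the same stratum. In a logistic model, omitting baseline variables that predict the outcome costs some power for the treatment effect. The margin here is thin: the design needs 892 per arm and plans 900. The Discussion also accepts that contamination between arms might dilute the effect. At stake is a small amount of power that the trial could have without collecting anything new.

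**Working it through.** **Inputs.** From Sample size: control rate p1 = 0.18, odds ratio 0.65, two-sided alpha 0.05, 900 per arm. From Statistical methods: logistic regression, with the decision taken on the odds-ratio interval. The strength of the baseline predictors is not given anywhere in the article, so it is varied as an assumption.

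**Step 1: reproduce the stated power.**

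- Intervention rate: odds = 0.65 × 0.18/0.82 = 0.14268, so p2 = 0.14268/1.14268 = 0.12487. The difference is 0.05513 and the mean rate is 0.15243.
- Required n per arm = [1.960·√(2 × 0.15243 × 0.84757) + 1.2816·√(0.1476 + 0.10928)]² / 0.05513² = (0.9963 + 0.6495)² / 0.003040 = 891.1, that is 892.
- Power at 900, pooled test: Φ[(0.05513 × 30 − 0.9963)/0.5068] = Φ(1.298) = 90.3%.
- Power on the log odds ratio scale, which is the scale of the planned decision: SE = √[1/(900 × 0.1476) + 1/(900 × 0.10928)] = 0.1330; z = 0.4308/0.1330 = 3.238; power = Φ(3.238 − 1.960) = 89.9%.

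The 90% is confirmed. It comes from an unadjusted comparison and does not rely on any covariate.

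**Step 2: add one baseline risk score.** The model is logit P(event) = a + c·treatment + b·x, with x standard normal and standing for the combined covariates. For each b, the values of a and c are solved so that the overall rates stay at 18% and 12.49%. The SE of c comes from the expected information with 900 per arm, and power = Φ(|c|/SE − 1.960). The AUC is that of the score in the control arm.

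| b | AUC | conditional OR | SE of log OR | power | efficiency ratio | n per arm for the planned power |
|---|---|---|---|---|---|---|
| 0 | 0.50 | 0.650 | 0.1330 | 89.9% | 1.000 | 900 |
| 0.25 | 0.57 | 0.648 | 0.1336 | 90.2% | 1.008 | 893 |
| 0.50 | 0.64 | 0.641 | 0.1352 | 90.8% | 1.032 | 872 |
| 0.70 | 0.68 | 0.632 | 0.1373 | 91.6% | 1.064 | 846 |
| 0.90 | 0.73 | 0.621 | 0.1401 | 92.6% | 1.105 | 814 |

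In the last row, for example, the expected z is about 0.477/0.140 = 3.404, and Φ(3.404 − 1.960) = 92.6%. The SE has risen from 0.1330 to 0.1401, but the log odds ratio has moved further (from −0.431 to −0.477), so the expected z rises from 3.238 to 3.404.

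Simulation with 3,000 trials per setting is consistent with this, given a Monte Carlo error of about 0.5 points per figure. Unadjusted and adjusted power were 89.5% and 89.5% at b = 0.25, 89.9% and 91.1% at b = 0.50, and 89.9% and 91.9% at b = 0.75.

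**Step 3: does the gain survive with site already in the model?** The article gives no site-specific rates. As an assumption, take six equal sites with log-odds spaced evenly from −0.8 to 0.8 and the same overall rates. The model with treatment and site has 90.9% power. Adding the score gives 91.2% at b = 0.25 and 93.3% at b = 0.90, gains of 0.2 and 2.4 points. The increment is about the same.

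**Step 4: is there room for the covariates?** Expected events are 900 × 0.18 + 900 × 0.12487 = 162 + 112 = 274. The model proposed below has 1 treatment, 5 site, 1 admission-type and 5 covariate coefficients, 12 in all, or 274/12 = about 23 events per coefficient.

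**The case against.** The strongest reply is that nothing here is wrong. Adjusting for exactly the factors that stratified the randomisation is a standard, valid analysis, and the sample size was computed without covariates and holds. That stands in full. A reader might infer that the trial is underpowered or its primary analysis flawed; the article does not support that.

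Three further inferences are tempting and also go too far:

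- **That strong predictors were ignored.** The Background calls them significant and gives no effect size or AUC. The Discussion reports that ADR prediction tools performed inadequately at these sites. That remark concerns correcting for differences in risk between clusters, so it does not show that the covariates are uninformative among patients within a site. It gives no support for calling them strong either.
- **That precision is being given away.** For the odds ratio the plan reports, adjustment widens the interval on the log scale. Only power improves, and the odds ratio becomes conditional on more covariates.
- **That the effect is expected to be diluted.** The Discussion says only that contamination might dilute it, and the assumed odds ratio is already weaker than in the earlier trial.

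Two more points stand in part. Completeness of every proposed covariate is not guaranteed, because the article does not say which baseline items count as necessary before allocation is released. Supportive adjusted analyses may also sit in an analysis plan not shown, and their absence here is no fault. But the covariates of the primary model are stated in this article, so the suggestion concerns a choice that has been made.

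**Conclusion.** The point holds as a cheap improvement to a valid plan. The article names predictors of its own outcome, has them or measures of them at baseline, and leaves them out of the primary model. For an assumed AUC between 0.57 and 0.73, including them raises power by about 0.2 to 3 points, from 89.9% to between 90.2% and 92.6%. That is equivalent to between 900 − 893 = 7 and 900 − 814 = 86 patients per arm. At the weak end the benefit is negligible.

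The size rests on the assumed AUC, on representing the covariates by a single normal score, on the planned 18% rate and odds ratio of 0.65, and on no attrition. The check with site in the model rests on an assumed spread of site rates.

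**What to change.** Before unblinding, change the sentence in Statistical methods so that the primary logistic model adjusts for the randomisation strata plus age, sex, number of active conditions, number of current drugs and Barthel Index. Barthel serves as the available measure of function, since no frailty scale is listed among the collected data. Enter the continuous variables as linear terms. Keep the strata-only model as a sensitivity analysis. Report a standardised (marginal) risk difference from the primary model beside the conditional odds ratio.

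The cost is a change of wording in the protocol or analysis plan; no additional data are needed. The downside is one of interpretation: the odds ratio is conditional on more covariates and lies slightly further from 1 than the strata-only one (0.648 to 0.621 against 0.650 over the assumed range). The standardised risk difference and the sensitivity analysis let readers see the effect on the other footing.

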### Sample size

In a recent single blinded trial of the manual application of STOPP/START criteria, conducted at the coordinating investigator site, the observed control group hospital-acquired ADR incidence was 21% compared to an ADR incidence of 11.5% in the intervention group, equivalent to an ADR odds-ratio of 0.45 [8]. This study had similar entry criteria and primary endpoints to the current trial, but differed in that the STOPP/ START recommendations were manually generated and then directly discussed and reviewed with the primary team by a specialist registrar (senior resident) in geriatric medicine. To be conservative, and in view of the more rigorous ADR adjudication processes, we have based our power calculations for the current trial on a lower control group event rate (18%) than that seen in our earlier trial, and we assume a reduced effect size (an odds ratio of 0.65) in order to reflect the potential reduced uptake of recommendations by clinicians. Based on these assumptions, using the method of Farrington and Manning for a trial to test the difference between two binomial events with a two-sided type 1 error rate of 0.05, we achieve 90% power with the proposed recruitment of 900 subjects per trial arm. The planned CONSORT flow diagram for the trial is shown in Fig. 3.

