Inappropriate prescribing and excessive polypharmacy are both linked to ADRs, but few interventions addressing these risks have been evaluated. A recent single centre clinical trial showed that the application of the ‘Screening Tool of Older Persons’ Prescriptions’ (STOPP) and ‘Screening Tool to Alert doctors to the Right Treatment’ (START) screening tools by an experienced geriatrician within 48 h of admission reduced incident in-hospital ADRs from 21.0 to 11.7% [8]. Patients recruited to this study were adults 65 years and older admitted acutely to hospital; patients were excluded if they were admitted directly to the intensive care unit, under geriatric medicine, old age psychiatry, clinical pharmacology or palliative medicine. Additional studies have shown that the manual (i.e. not delivered by software) application of STOPP/START criteria improves medication appropriateness [9, 10] and reduces the risk of falls [11]. However, these trials have been single centre and unblinded. Furthermore, the lack of sufficient geriatric medicine specialists limits the applicability of this manual approach. To overcome these limitations, a novel software tool called SENATOR (Software ENgine for the Assessment and optimisation of drug and non-drug Therapy in Older peRsons) was developed, which automatically provides individualized STOPP/START and other relevant recommendations based on standardized inputs. Given the support in the literature for the efficacy of the STOPP/START recommendations, we decided to conduct a pragmatic trial to quantify the effectiveness of providing the individualised SENATOR software report to the participating patient’s attending hospital clinician for review and implementation as he/she judges appropriate compared to usual clinical care, with the aim of reducing in-hospital ADRs amongst older adults in a real world setting across 6 European hospitals.

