We had initially proposed a cluster randomized trial adjusting for difference in baseline ADR risk using an ADR prediction tool such as the previously validated Gerontonet ADR Risk Scale [6]. This approach had the specific advantage of limiting contamination between the intervention and control arm, especially if it transpired that the same investigator was simultaneously attending a subject in both arms of the trial. However, in our feasibility study we discovered a very large degree of heterogeneity in ADR rates between different sites and between specialities within individual sites. Some of this heterogeneity may have resulted from initial limited standardization of our ADR reporting and adjudication processes and from sampling variability given the limited sizes of individual samples as well as real substantive differences between sites. Furthermore, we found that within our population the ADR predictions tools were inadequate for correcting for the between-cluster variability in baseline ADR risk. This made it impossible to exclude the possibility that any observed differences in the proposed trial might not simply be the consequence of an unequal distribution of baseline ADR risks across sites. We therefore adopted an individual level randomization, accepting that a degree of cross arm contamination might dilute the perceived effect size. However, even in a cluster design this effect is not fully prevented because junior medical staff routinely migrate between various specialities within a hospital and senior clinicians typically cross cover other specialist services at weekends and when working on-call outside of regular daytime hours.

The assessment of ADRs gives rise to several methodological complexities that have not previously been widely discussed in the literature. It is necessary to distinguish between prevalent (pre-dating the hospitalization and on occasion necessitating it) and incident ADRs, which occur during the index hospital stay. These are likely to differ in their characteristics, risk factors and consequences, making the distinction particularly relevant for ADR risk prediction tools. From the SENATOR trial viewpoint, it is necessary to exclude ADRs occurring prior to randomization; therefore outcomes in this trial will only include in-hospital incident ADRs that occur post randomization, but we also take account of whether identification and response to prevalent ADRs is influenced by study intervention.

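### The prior trial's odds ratio is misstated (0.45, where its rates give 0.49 to 0.50), so the discount to 0.65 is smaller than presented, and the plan does not say whether 0.65 is net of contamination

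*Protocol article*

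**What the plan says.** The Sample size section takes its benchmark from a prior trial of manually applied STOPP/START criteria. It gives a control rate of 21%, "compared to an ADR incidence of 11.5% in the intervention group", and describes the pair as "equivalent to an ADR odds-ratio of 0.45". The Background cites the same reference but says that the intervention "reduced incident in-hospital ADRs from 21.0 to 11.7" per cent.

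Under the banner of being conservative, the Sample size section then makes two choices: a control rate of 18%, and a smaller effect ("we assume a reduced effect size (an odds ratio of 0.65"). The reason given for the smaller effect is that clinicians may take up fewer recommendations. With a two-sided 5% test, 900 per arm is said to give 90% power.

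The Discussion explains why individual randomization replaced a cluster design, "accepting that a degree of cross arm contamination might dilute the perceived effect size". The Sample size section does not mention contamination. The primary logistic model is fixed as "adjusting for strata used in the randomization (medical versus surgical admissions and study recruitment site"), with no other covariates named.

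**The concern.** The stated odds ratio does not follow from the rates beside it, and the two sections disagree on one of those rates. The figure matters because it is the yardstick against which 0.65 is called a reduced effect. If the prior effect was weaker than 0.45, less has been taken off for caution than the reader is led to believe.

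A second gap lies in the same rationale. The planned design can dilute the effect in two ways: fewer recommendations adopted in the intervention arm, and advice carried over to control patients by shared clinicians. Only the first is given as a reason for 0.65. What is at stake is how a reader judges the caution of the target effect and the conditions under which the 90% holds. The number of patients is not at stake.

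**Working it through.** **Inputs.** Sample size section: prior rates 21% and 11.5%, prior odds ratio 0.45, planning control rate 18%, planning odds ratio 0.65, two-sided alpha 0.05, 900 per arm, 90% power. Background: 21.0% and 11.7%. Randomization section: 1:1 allocation.

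**1. The plan's own power.**
- Intervention odds = 0.65 × 0.18/0.82 = 0.1427, so the rate is 0.1427/1.1427 = 12.49%, a difference of 5.51 points.
- For a null difference of zero, the Farrington and Manning method should be essentially the pooled two-proportion test: power = Φ{[d − 1.96·√(2p̄(1−p̄)/n)] / √([p₀(1−p₀) + p₁(1−p₁)]/n)}.
- With d = 0.0551, p̄ = 0.1524 and n = 900: (0.0551 − 0.0332)/0.0169 ≈ 1.30, which gives 90.3%.
- Exactly 90% needs 892 per arm. Unpooled, log-odds-ratio and continuity-corrected versions give 90.4%, 89.9% and 89.1%.
- The stated 90% reproduces, and 0.45 does not enter the calculation.

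**2. The prior odds ratio.**
- With 11.5%: (0.115/0.885)/(0.21/0.79) = 0.489.
- With 11.7%: (0.117/0.883)/(0.21/0.79) = 0.498.
- Most favourable rounding (11.45% against 21.5%): 0.472.
- An odds ratio of 0.45 at 21% would need an intervention rate of 10.7%.
- The relative risk reduction is 1 − 11.5/21 = 0.452. It may have been labelled as an odds ratio, but that is inference.

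**3. Size of the discount on the log-odds-ratio scale.**

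| Prior odds ratio | Share kept by 0.65 | Cut |
|---|---|---|
| 0.45 (stated) | ln 0.65/ln 0.45 = 54% | 46% |
| 0.489 | ln 0.65/ln 0.489 = 60% | 40% |
| 0.498 | ln 0.65/ln 0.498 = 62% | 38% |

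**4. Sensitivity to contamination (assumed levels).** The article gives no level. Suppose that 0.65 is the effect before contamination and that a share c of it reaches controls, so that the control rate is 18% − c × 5.51 points. The intervention rate stays at 12.49%.

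| c (assumed) | Control rate | Power at 900 per arm | Per arm for 90% |
|---|---|---|---|
| 5% | 17.72% | 87% | 981 |
| 10% | 17.45% | 84% | 1,085 |
| 20% | 16.90% | 75% | 1,352 |

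**5. What covariates could add.** Under assumed prognostic strength, simulation puts the efficiency gain from a few baseline predictors at roughly 3 to 10%. Returning to 90% would need 1,085/900 − 1 = 21% more information at 10% contamination, and 1,352/900 − 1 = 50% more at 20%.

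**The case against.** The strongest reply is that the slip changes nothing in the design. Had 0.49 been printed, the sample size, the power and the contamination question would all be the same. This stands. The target of 0.65 is also still a clear reduction, 38 to 40% of the corrected log-odds ratio. It is accompanied by a second cautious step, the lower control rate: at 21% and 0.65, 900 per arm would give about 93.5%. That stands too. It limits the error to the description of the discount.

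It could also be said that 0.45 is an adjusted estimate. The cited study is not at hand, so this cannot be excluded, but the article's wording equates 0.45 with the two crude rates.

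Three stronger readings are tempting, and the article does not support them.
- **True power is 82 to 84%.** A reader might apply the 54% retention to the corrected odds ratio, reach a target of 0.68 to 0.69, and conclude this. The article states no proportional rule. It simply assumes 0.65.
- **The odds-ratio error leaves no room for contamination.** The two points are independent. A planning odds ratio is the difference to be detected between the arms, and 0.65 may already be net of contamination. The article does not settle this. A sample size that only just meets its power target is ordinary practice.
- **Covariates would win back power lost to contamination.** A gain of 3 to 10% falls well short of the 21% or 50% needed at the 10% and 20% levels. The Discussion also reports that ADR prediction tools corrected poorly for differences in baseline risk between clusters, which argues for modest expectations.

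**Conclusion.** The stated prior odds ratio is wrong for the rates given with it. It should be 0.49, or 0.50 if 11.7% is the right rate, and the two rates for one study must be reconciled. The planning value of 0.65 keeps about 60 to 62% of the prior log-odds ratio, not 54%, so the caution is overstated by a modest amount. The 900 per arm and the 90% power stand.

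Separately, the rationale for 0.65 names uptake alone although contamination is accepted elsewhere in the article. The 90% is therefore conditional on 0.65 being the net effect after contamination. The figures of 87%, 84% and 75% rest on assumed leakage of 5%, 10% and 20% and on 0.65 being the effect before contamination. They illustrate sensitivity and do not estimate this trial's power.

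The arithmetic and the conflict between the two rates are certain. The practical weight is that of a correction to the stated justification, with no change to the design.

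**What to change.** In the Sample size section and the Background:
1. Check the prior trial's intervention rate and use one figure, 11.5% or 11.7%, in both places.
2. Restate the prior odds ratio as 0.49 or 0.50 accordingly. If 0.45 is an adjusted estimate, say so and do not equate it with the crude rates.
3. Describe 0.65 as retaining about 60% of the prior log-odds ratio.
4. State that 90% power is conditional on 0.65 being net of both lower uptake and contamination. If sensitivity figures such as 87%, 84% and 75% are shown, label the contamination levels as assumptions.

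These are text changes. They add no patients, and the power statement becomes slightly less favourable.

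As an optional improvement, pre-specify a few baseline predictors in the primary logistic model besides the strata: age, sex, number of drugs, number of conditions and Barthel Index. The Background names age, sex, multimorbidity and polypharmacy as ADR predictors. The Data management section lists medical history, medications and Barthel as collected. It does not itemise age and sex, which are presumably recorded. The expected gain is roughly 3 to 10% in efficiency, depending on how prognostic these variables prove. The cost is that the odds ratio becomes conditional on those covariates as well as the strata, so it is less directly comparable with the crude planning value.
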